### ***Therapist observations and evaluation***

Therapist observations and evaluation of the child’s engagement, participation, persistence, task direction and task pleasure will occur during therapy sessions. This requires therapists to complete two Likert scales on task persistence and affect at the end of each therapy session. To assist in completing these scales the therapist will observe the following behaviours during sessions:

a. Persistence with a challenging problem, skill or task. Observation of the amount of task directed – is important in evaluating persistence. Greater persistence indicates greater mastery behaviour – which includes trying successfully or unsuccessfully to solve the problem or master the task motivation [110].

b. Embracing rather than avoiding challenge. Choosing challenging tasks in preference to easy ones indicates greater mastery motivation [110].

c. Displays of positive affect (smiling, pleasure, pride) associated with persistence. Positive displays of mastery (task) pleasure indicate higher levels of motivation [110].

d. Prematurely requesting help and avoiding challenges which indicate lower mastery motivation [110]

e. Any negative reactions and emotional responses to failure.

At the end of every therapy session therapists will evaluate the most common or predominant motivational behaviour observed. This will be measured on two scales:

i. *The Task Directed and Persistence Scale*: determines on a scale of 1 to 9 how task directed, persistent, goal focused and motivated a child was during the therapy sessions

ii. *The Child*’*s Affect Scale*: determines on a scale of 1 to 9 the level of positive affect demonstrated by a child during therapy sessions.

### ***Post intervention interviews***

The above measures will be supplemented with individual semi structured interviews post training to identify experiences of children participating in COMBiT, to gain insights into their experience of the day camp. Video footage of training sessions will be presented to facilitate interviews and discussions with children and their primary caregivers. Interviews will be videorecorded and transcribed verbatim.

## Blinding

Functional MRI data will be qualitatively analysed by neurologists masked to group allocation. Paediatric neurologists with fMRI training will independently rate scan quality (0–5), region of activation, change over time and patterns of reorganisation. Data for AHA and MUUL will be rated from videos masked to order and group allocation.

## Adverse events

Any minor and major events associated with intramuscular BoNT-A injections prior to the training study or due to either training model will be screened at 2 weeks by open-ended questions. If temporary weakness occurs following intramuscular BoNT-A injections, this can be addressed during the training programs. Any adverse events or unintended effects detected will be reviewed by a Rehabilitation Physician.

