### Randomisation

Following baseline assessments, children will be randomised within matched pairs to receive either COMBiT or standard care. To maximise homogeneity of the sample and minimise group differences at baseline, matching in pairs will be completed according to age (12 month bands), gender, and Manual Ability Classification System (MACS) level [30]. Treatment allocation will be recorded on a piece of folded paper inside a concealed opaque envelope. Using a sequence of computer-generated random numbers the number “1” or “2” will be allocated to each member of the pair. As each pair is randomised, they will be allocated the next consecutive envelope, which will be opened by non-study personnel who will read and record the treatment allocation. Study personnel will be informed of group allocation.

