COMBiT will be conducted over two weeks of the school holidays in a “day camp model”. Participants will attend a community facility “Flipside Circus” for six hours a day, five days a week from 9am to 3pm. In total, 45 hours of the day camp program will directly target upper limb training, and 10 hours will provide indirect use of the UL in more general gross motor upper limb activities. For both mCIMT and BIM training, the content will include intensive activity based practice, circus activities as well as self-care and recreational activities. The group will be led and supervised closely by five to seven therapy staff to achieve a ratio of one trainer to two children. Five core occupational therapists and one physiotherapist will plan and lead all intervention groups. Daily grading of activities and modification of tasks for the participants in each group will be performed by the core therapists. Tasks and activities will focus on reducing upper limb activity limitations identified at baseline assessment and target three occupational performance goals identified by the parents and/or child. Planning activities for each group will require task analysis, and develop guidelines for grading to challenge children with varying capabilities. Specific details of the content of the COMBiT weekly program contents are presented in Additional file 1: Table S1. Prior to commencement of the daily program, staff will be briefed and given specific tasks with written instructions outlining how each activity will be performed for the specific children they are supervising. Professional circus trainers will lead the two hour circus workshops. The core therapy team will meet with the circus trainers to design these programs and at the end of each session to discuss and modify the program as required and provide guidance to grading of tasks for participants. A debriefing session for the entire COMBiT group with staff members and separately for the staff and volunteers will be conducted at the conclusion of each day. The core therapy team will also meet daily to review individual participants’ goals and continually grade their program. A daily record of attendance will be kept and anecdotal information from the day will also be recorded.

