#### ***Study duration***

Children will be recruited in blocks of 24 to 26 children at six monthly intervals to enable sessional testing of fMRI and training. The children will attend day camps during a holiday period. Recruitment will take 12 months, as suitable candidates could be drawn from our QCPRRC register (n=180 potential children). Potential participants can receive upper limb intramuscular BoNT-A injections prior to study entry as part of clinical practice. Entry into the study will be delayed for six weeks post injection for those whom have received intramuscular BoNT-A injections in the forearm to reduce spasticity.

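### The adverse event screen is defined by presumed cause and uses open questions, so recorded harms are liable to differential ascertainment between the closely observed camp arm and the largely home-based arm

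*Protocol article*

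**What the plan says.** The Adverse events section names two kinds of event to be screened. The first is "Any minor and major events associated with intramuscular BoNT-A injections prior to the training study". The second is events "due to either training model will be screened at 2 weeks by open-ended questions". It then adds: "Any adverse events or unintended effects detected will be reviewed by a Rehabilitation Physician". It does not say who asks the questions, who decides that an event is linked to training or BoNT-A, or from what date the two weeks run.

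On knowledge of treatment, the Randomisation section says: "Study personnel will be informed of group allocation". The Blinding section states masking for two sets of ratings: "Functional MRI data will be qualitatively analysed by neurologists masked to group allocation" and "Data for AHA and MUUL will be rated from videos masked to order and group allocation".

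On observation, the section describing COMBiT sets out six-hour days, five days a week for two weeks, with about one trainer to two children, daily debriefings and a daily log in which "anecdotal information from the day will also be recorded". The sections on study interventions and standard care set out six weekly sessions of 1.5 hours, plus 30 minutes of home practice six days a week for 12 weeks.

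On BoNT-A, the Study duration section says of injected children: "Entry into the study will be delayed for six weeks post injection". Randomisation follows baseline assessment.

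**The concern.** A harms screen should first capture what happened and then ask why. Here the cause is part of the definition of what is screened. In a trial where those answering know the treatment, the decision that an event was due to training is open to expectation. Open questions give no common prompt to offset this.

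The two arms also offer very different chances of an event being seen. A fall, a sore arm or an episode of distress at the camp happens in front of therapy staff and in an obvious training setting. The same event during half an hour of practice at home may not be mentioned, or may not be thought of as due to training. If so, recorded harms would tend to look higher in COMBiT for reasons unrelated to the training itself. A larger sample would not remove that tendency, and events never recorded cannot be recovered at analysis.

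At stake is the description of harms, not the efficacy result. The Background presents COMBiT as a possible model of care if it proves superior and sustained, so readers will set the harms of the two arms side by side whether or not a formal test is planned.

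**Working it through.** The protocol gives no adverse event rate and no harms calculation, so there is no stated figure to reproduce. The check is a reading of the rule, followed by arithmetic on training hours.

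**Step 1: what the rule covers.**
- Linked to earlier BoNT-A: inside the screen.
- Due to either training model: inside the screen.
- Neither link made by anyone: not covered by the screening sentence.
- The physician's review applies to events already detected. It widens what is reviewed but does not state any further way of finding events.

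**Step 2: planned hours with staff present.**
- COMBiT: 10 days × 6 h = 60 h of attendance. The 45 h direct and 10 h indirect training are both delivered within the supervised camp, so the supervised share of training is 100%.
- Standard care, therapist sessions: 6 × 1.5 h = 9 h.
- Standard care, home practice: 0.5 h × 6 days × 12 weeks = 36 h.
- Standard care, total: 9 + 36 = 45 h. Therapist share 9/45 = 20%; home share 36/45 = 80%.

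**Step 3: the same share at the screen itself.** If the two weeks run from the start of training (an assumption), standard care has by then had 2 to 3 sessions (3 to 4.5 h) and 2 × 6 × 0.5 = 6 h of home practice. The therapist share is 3/9 = 33% to 4.5/10.5 = 43%. The contrast with the camp is smaller than over the whole programme, but it remains.

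**Step 4: what this could do (illustration only).** Assume that events occur at the same rate per training hour, that every event in a staffed hour is noticed and attributed, and that a fraction *q* of events in home practice is. The documents do not give *q*. The proportion captured in standard care over the full programme is (9 + 36*q*)/45, against 1 in COMBiT:

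| *q* | Captured in standard care |
|---|---|
| 1 | 45/45 = 100% |
| 0.75 | 36/45 = 80% |
| 0.5 | 27/45 = 60% |
| 0.25 | 18/45 = 40% |
| 0 | 9/45 = 20% |

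On the two-week basis of Step 3, *q* = 0.5 gives (3 + 3)/9 = 67% to (4.5 + 3)/10.5 = 71%. The arms are equal only if home events are noticed and attributed as readily as camp events. The rule contains nothing to bring that about.

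**Step 5: BoNT-A.** Injection precedes study entry by at least six weeks and randomisation comes after baseline, so the exposure precedes allocation. It is named in the same sentence and covered by the same screen as training events, but the text describes no joint count.

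**The case against.** The strongest reply is that the section never says that only attributed events are collected, describes no causality decision before recording, and sends any detected event to a physician. An open question does not itself filter by cause, and the same method applies to both arms. Hours with a therapist are not a measure of how well adverse events are found, and the camp's daily notes are nowhere called a source of adverse events. No between-arm analysis of harms is planned. A condensed article may also leave forms, prompts and masking of the relatedness review to the full protocol.

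Much of this stands and limits the point. The absence of a stated masking rule or checklist is not a defect in an article of this kind. The share of hours shows unequal opportunity for observation, not a measured bias. What remains is that the article does state a rule, that the rule identifies events by cause, and that the physician sentence starts from what has been detected.

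A reader might go further and infer that BoNT-A events and training events are mixed in one count. The text names them separately and describes no shared record or pooled total. Earlier BoNT-A use is balanced on average by randomisation, so even pooling would mainly add noise; the number of injected children is not given, so no chance imbalance can be worked out. Nor can onset be placed before randomisation for every such event, since the section itself allows for weakness during training.

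A reader might also conclude that harms cannot be compared fairly at all. That is too strong: the documents support a risk of differential ascertainment of unknown size.

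Whether a single screen at two weeks suits a 12-week programme is a separate question. A later or repeated screen with the same wording would still miss events that nobody attributed.

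**Conclusion.** The point holds in a limited form. The stated screen is defined by presumed cause and relies on open questions in an open trial, where staff are present for all of the training in one arm and for 20% of planned hours in the other (33% to 43% by week two, if counted from the start of training). Recorded harms are therefore liable to differential ascertainment, most plausibly towards more recorded events in COMBiT.

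This rests on the plain reading of the screening sentence, on families knowing which programme their child attends, and on the judgement that events are noticed and attributed more readily at a staffed camp than at home. The size is unknown, and the table above shows only the range under stated assumptions. The sample size, the primary outcomes and their masked ratings are unaffected. The change is worth making because it is cheap beforehand and impossible afterwards.

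**What to change.** Reword the Adverse events section along these lines:

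1. All adverse events from the start of training are recorded in both arms, whatever their presumed cause.
2. They are elicited with the same short set of prompts in both arms (for example pain in the hand or arm, skin problems, falls or injury, fatigue, distress or refusal), followed by one open question.
3. Relatedness is judged after recording by the Rehabilitation Physician who already reviews events.
4. Events linked to BoNT-A given before randomisation are tabulated separately from training events.

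The cost is a change of wording and a one-page form, with no new visits or staff. More minor, unrelated events will be recorded and reviewed. Common prompts will reduce the difference in observation between camp and home but will not remove it, so the report should still say that the arms were observed to different degrees.

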### Study interventions

For the COMBiT day camp group, we plan to provide treatment in groups of 10–15 children over ten days. The initial five consecutive days will focus on mCIMT. After a weekend, BIM will be provided for the next five consecutive days. Therapy will comprise 45 hours direct upper limb training and 10 hours of indirect training in more general gross motor upper limb activities. COMBiT will have a novel circus theme. This intensive COMBiT therapy will be compared to standard care which involves individually tailored therapy in a distributed model for 1.5 hours per week for six weeks. This involves six hours individual therapy with OT/PT and three hours of home program demonstration (nine hours direct UL therapy). The home programs (completed by participants in their home/community environment) will comprise 30 minutes daily home practice six days/week for 12 weeks (36 hours indirect UL therapy). The COMBiT and the standard care programs will have the same dosages of upper limb therapy (COMBIT: 45 hours direct UL training; Standard care (SC): nine hours direct UL training and 36 hours indirect UL therapy). They will differ by (i) delivery method (block, group model versus distributed individualised model) (ii) varied construct (mCIMT versus goal directed training) and (iii) different environment.

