#### ***(ii) Standard care upper limb rehabilitation***

Standard care comprises an individualised and distributed model of occupational therapy upper limb training which consists of six sessions of 1.5 hours of individual direct therapy provided in a hospital or community setting over six weeks in combination with a 12 week home program. The weekly 1.5 hour sessions comprise one hour of direct therapy, and half an hour for home program development, demonstration and training with a total dose of nine hours of direct therapy. Families will be provided with a home program to practice goal areas for 12 weeks from the commencement of individual therapy sessions (30 minutes daily practice for six days/week for 12 weeks) for a total dose 36 hours of indirect UL therapy for the standard care group. The total anticipated therapy dose for standard care including direct therapy and home program practice is 45 hours of training.

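### The one stated adverse event screen is at 2 weeks with no stated starting point; counted from the start of training, it covers all of COMBiT but only about 17–20% of standard care

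*Protocol article*

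**What the plan says.** The Adverse events section sets one time and one method for both injection-related and training-related events. Events "due to either training model will be screened at 2 weeks by open-ended questions". It then adds: "Any adverse events or unintended effects detected will be reviewed by a Rehabilitation Physician". It gives no starting point for the 2 weeks and describes no other route of detection.

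The two programmes differ sixfold in length:

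- **COMBiT.** "COMBiT will be conducted over two weeks of the school holidays in a" day camp format. On dose, the Study interventions section says: "Therapy will comprise 45 hours direct upper limb training and 10 hours of indirect training in more general gross motor upper limb activities".
- **Standard care.** The section on standard care upper limb rehabilitation gives "six sessions of 1.5 hours of individual direct therapy provided in a hospital or community setting over six weeks", with a home programme of "30 minutes daily practice for six days/week for 12 weeks" that starts together with the sessions.

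The Abstract places outcome assessments at 13 weeks after commencement and at 26 weeks. The Concurrent therapies section lists what is documented at each follow-up (other therapies, changes in spasticity medication, lower limb interventions). Adverse events are not on that list. For children who have had BoNT-A, the Study duration section says: "Entry into the study will be delayed for six weeks post injection".

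**The concern.** A single early screen applied to programmes of 2 and 12 weeks observes different fractions of each. On the natural reading, every COMBiT child is asked after finishing the programme, and every standard care child is asked after about a fifth of it or less. A later tabulation of events by arm would then tend to show more events under COMBiT even if the two programmes were equally safe.

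Routine contact pushes the same way. Camp staff keep daily attendance and anecdotal notes, whereas most standard care hours are practised at home.

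Two things are at stake: the fairness of any by-arm safety statement about a model that the Background presents as a candidate for wider use, and information on late events in children.

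**Working it through.** **Inputs, all from the protocol article.** COMBiT: 2 weeks, 45 h direct plus 10 h indirect. Standard care: six weekly sessions of 1.5 h, and home practice of 0.5 h on 6 days a week for 12 weeks, both starting together. Screen: 2 weeks. Assessments: 13 and 26 weeks. Start of training: within one month of baseline. Entry: six weeks after any BoNT-A injection.

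**Step 1. Reproduce the stated standard care dose.** 6 × 1.5 = 9 h; 0.5 × 6 × 12 = 36 h; 9 + 36 = 45 h. This matches the article.

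**Step 2. Coverage at week 2, counted from the start of training.** The standard care dose share by week w is (1.5 × min(w, 6) + 3 × min(w, 12)) / 45.

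| | Standard care | COMBiT |
|---|---|---|
| Dose | (3 + 6)/45 = 9/45 = 20.0% | 55/55 = 100% |
| Calendar time | 2/12 = 16.7% | 2/2 = 100% |
| Therapist-led hours | 3/9 = 33.3% | 100% |

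Ten weeks of standard care (12 − 2) follow with no described screen.

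**Step 3. Other starting points.**

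- *Baseline:* training may start up to about 4 weeks later, so coverage is 0–100% of COMBiT and 0–20% of standard care.
- *Injection:* the screen falls before study entry and covers no training in either arm.
- *End of each programme:* coverage is 100% in both arms. The screen then falls at about week 2 + 2 = 4 in COMBiT and 12 + 2 = 14 in standard care, so the observation windows differ. Week 14 matches no planned assessment and comes after the return to regular therapy that follows the 13-week visit.

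**Step 4. Illustration of the possible distortion.** The article gives no event rates, so this step rests on assumptions: equal true risk p per programme, constant hazard, and capture only up to the screen at week 2 of training. With covered fraction f, the observed standard care risk is q = 1 − (1 − p)^f. The apparent COMBiT to standard care risk ratio is p/q, where the truth is 1.

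| p | f | q | Expected counts of 25, COMBiT v standard care | p/q |
|---|---|---|---|---|
| 0.10 | 2/12 | 0.017 | 2.5 v 0.44 | 5.74 |
| 0.10 | 0.20 | 0.021 | 2.5 v 0.52 | 4.80 |
| 0.20 | 2/12 | 0.037 | 5.0 v 0.91 | 5.48 |
| 0.20 | 0.20 | 0.044 | 5.0 v 1.09 | 4.58 |
| 0.50 | 2/12 | 0.109 | 12.5 v 2.73 | 4.58 |
| 0.50 | 0.20 | 0.129 | 12.5 v 3.24 | 3.86 |

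Across p from 10% to 50%, the apparent ratio runs from about 3.9 to 5.7.

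**Step 5. Effect of the remedy.** By week 13 the standard care share is (9 + 36)/45 = 100%, the same as COMBiT, over an identical calendar window.

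**The case against.** Four points can be made for the plan.

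- **The contrast depends on an unstated starting point.** A reader might take 100% against 20% as a fact of the design. It is not: one reading gives full coverage in both arms. This stands, and the figures are conditional. It does not clear the text, because the starting point is itself missing and every other reading has a difficulty of its own (Step 3).
- **No safety comparison is planned.** A reader might infer that a planned safety comparison is biased. The hypotheses do not mention safety, and the Statistical analyses section contains no between-arm analysis of adverse events. The section describes screening followed by physician review. A screen at the same time after the start also gives both arms the same calendar window, and misleads only if it is read as whole-programme risk. This stands: the bias belongs to any by-arm count that someone later makes.
- **Silence in a condensed article is weak evidence.** A reader might infer that later events will go uncollected. The text does not say that the screen is the only one, it sets no time limit on review of detected events, and the full protocol may say more. What can be said is that no later questioning is described. The point does not rest on omission alone, since the article states one common time for two programmes of very different length.
- **BoNT-A.** A reader might infer that one time point cannot serve both injection and training events. That goes too far. The injections precede the study, so the question about them is retrospective, and it can still be answered at least 6 + 2 = 8 weeks later, if with weaker recall.

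**Conclusion.** The point holds in conditional form. The only stated adverse event screen is at 2 weeks from an unspecified start, for programmes of 2 and 12 weeks. If the 2 weeks run from the start of training, the screen covers all of COMBiT but 16.7% (time) to 20.0% (dose) of standard care. Any by-arm event count would then be subject to unequal ascertainment, and later events may be missed. The apparent risk ratios of 3.9 to 5.7 show what could happen under the assumed risks, constant hazard and capture limit; they do not predict this trial. No efficacy result, hypothesis or planned analysis is affected. The change is worth making because it is cheap and improves safety information on children. The timing of BoNT-A questions is a minor side issue.

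**What to change.** 1. State what the 2 weeks are counted from.
2. Keep that screen, and ask the same open-ended adverse event questions in both arms at the existing 13- and 26-week assessments.
3. If events are reported by arm, tabulate them over the common window of weeks 0 to 13, and show weeks 13 to 26 separately, since children return to their regular therapy after the 13-week visit.
4. As a minor addition, ask about events after BoNT-A, with their dates, at baseline, which is at least six weeks after injection.

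The cost is a few minutes at visits already planned. No treatment, visit schedule or sample size changes.
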